### Sample size calculation

This is a pilot study to assess the efficacy of a smartphone-based intervention. To date, there has been no study evaluating the use of a smartphone app to improve NOAC adherence in Korea. Thus, a precise sample size calculation was not available. We assumed that drug adherences would be 90% in the control group and 95% in the intervention group according to the previous study.^26^ A sample size of 234 patients in each group achieves 95% power to detect a mean difference of 5.0 with a known SD of differences of 15.0 and a significance level (alpha) of 0.05, using a two-sided paired z-test. Considering drop-out rate of 4%, we finally planned to enrol 500 patients (250 patients in each group). We expect this pilot study will provide valuable information regarding the appropriate sample size, recruitment rate, study period and data management process, etc, for assessing the feasibility of the full-scale study we are planning further. And it also would allow to identify potential practical problems of whole research process.

### Statistical analysis

Categorical variables will be presented as numbers and frequencies, whereas continuous variables will be presented as means±SD. The Student’s t-test and Kruskal-Wallis test will be used to compare continuous variables depending on the presence of normally distributed variables. The χ^2^ test will be used to compare categorical variables. A p<0.05 was considered significant. The analysis would be performed according to the intention-to-treat principle. The standard regimen of edoxaban is once daily. The primary endpoint of edoxaban adherence will be calculated by pill count as shown below.

$$Pillcountadherence(\%)=\;\frac{Numberofpillsdispensed-Numberofpillsremaining}{Numberofdaysbetweendispensingdateandfollowupdate}\times 100$$

Since new drug users might have a lower adherence than continuous users, subgroup analysis will also be performed on the new and continuous users. To evaluate the feasibility and efficacy of the smart phone application, further analysis can be performed according to the frequency of the smart phone application use. The secondary endpoints of adverse events will be compared with the Kaplan-Meier curve analysis. A log rank test will be used to evaluate the significance of the difference between the two groups. Statistical analysis will be performed using IBM SPSS Statistics for Windows V.16.0 (IBM) and R software V.4.0.3.

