## Methods and analysis

### Study design

The Adhere-App (Self-awareness of Drug Adherence to Edoxaban Using an Automatic App. Feedback System) study is a multicentre, randomised, open-label and group-comparison trial to assess the effect of using a smartphone app to improve drug adherence (figure 1). A total of 10 tertiary university hospitals in Korea will participate in this study. The study participants will be randomised to a smartphone app-conditioned feedback group or a conventional treatment group. Every patient will receive education on AF and the importance of anticoagulation therapy. Additionally, the intervention group will be educated on the use of the smartphone app coupled with BP and HR measurement using an automatic BP measuring machine. Study visits will be performed at baseline, 3 months and 6 months (figure 2). When clinical visits are not possible due to the inevitable situation, the patient’s condition and survey data can be collected by telephone visit. This study was registered in the International Clinical Trials Registry Platform on 20 February 2020. However, initiation was delayed due to COVID-19 pandemic. As of 24November 2021, 80 patients were enrolled.

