### Patient recruitment and randomisation

Potential participants will be any patients visiting the clinic for AF management. After a comprehensive interview, written informed consent will be obtained from all eligible participants. Eligible participants will be asked to complete a baseline survey covering demographics and cardiovascular comorbidities. The eligible participants will then be randomly assigned to either the intervention group or the conventional treatment group in a 1:1 ratio using a web-based central randomisation service (http://matrixmdr.com/). Allocation concealment would be ensured, as the service would not release the randomisation results until the patient has been enrolled into the trial. Due to the nature of the intervention, it is not possible to blind participants to group allocation. All participants will be informed that the information on edoxaban adherence will be collected for analysis.

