### Study endpoints and follow-up

The primary endpoint is edoxaban adherence by pill count measurement at second (3 months) and third (6 months) visits. All patients will be asked to bring their remaining pills at each clinical visit. Secondary endpoints are clinical composite endpoints, including stroke, systemic embolic event, major bleeding requiring hospitalisation or transfusion, or death during the 6 months of follow-up by electronic medical records. The primary and secondary endpoints will be compared between smartphone app-conditioned feedback group and control group. An additional predefined observational parameter is symptom change related to BP (both systolic and diastolic) and HR. Clinical research coordinators will ask symptoms as an open question and each investigator will determine whether the symptom is related with BP and HR change. The study participants would be followed up relatively short period (6 months) and the protocol of current research carries only minimal risk. Thus, data monitoring committee and interim analysis plan would not be established.

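### Primary adherence is two pill counts per patient from 10 hospitals, but the only tests named take one value per patient, so a single-visit test leaves out randomised patients whose other count is held

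*Protocol article*

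**What the plan says.** All statements are in the protocol article.

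- Study endpoints and follow-up: "The primary endpoint is edoxaban adherence by pill count measurement at second (3 months) and third (6 months) visits". Patients are asked to bring leftover pills to their clinic visits.
- Study design: "A total of 10 tertiary university hospitals in Korea will participate in this study". The trial is open-label. A telephone contact may replace a clinic visit that cannot take place. It is described as collecting the patient's condition and survey data; a pill count is not listed.
- Patient recruitment and randomisation: patients are allocated individually "in a 1:1 ratio using a web-based central randomisation service". No stratification by hospital is stated.
- Statistical analysis: the Student's "t-test and Kruskal-Wallis test will be used to compare continuous variables", with the choice between them resting on normality. Also: "The analysis would be performed according to the intention-to-treat principle". The adherence formula gives one percentage per interval from dispensing to follow-up. The section does not say how the two visits form one comparison.
- Sample size calculation: the assumption is that "drug adherences would be 90% in the control group and 95% in the intervention group", with an SD of 15, 95% power, 234 patients per group and 4% dropout.

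**The concern.** Each patient should supply two adherence values and belongs to one of 10 hospitals, yet the tests named for continuous data use one value per patient from a single pool. Run at one visit, such a test includes only patients with a count at that visit. A patient with a 3-month count but no 6-month count then drops out of the 6-month comparison, although the article promises intention to treat.

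This matters if patients who lack the later count are mostly those who adhered poorly earlier, and if the pattern differs by arm. The mean among those counted is then too high in the affected arm. In the control arm this hides part of the app's effect; in the app arm it would flatter the app. The design makes such a pattern plausible: the count depends on bringing pills to the clinic, a telephone contact is not said to replace it, and patients know their allocation. A patient can stay in follow-up and still have no count, so the 4% dropout is not an upper limit on missing counts.

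A second, smaller matter is that differences between hospitals stay in the error term.

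**Working it through.** **The plan's own figure.** Inputs from Sample size calculation: difference 5, SD 15, two-sided alpha 0.05, power 95%. Two independent groups with one value per patient: n = 2 × (15/5)² × (1.960 + 1.645)² = 233.9, so 234 per group, as stated. (The article calls the test paired; a true paired z-test would need 117 pairs.) With 4% dropout, 250 × 0.96 = 240 per arm and power is 95.5%. The planned size thus rests on one value per patient and is adequate on its own inputs.

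**Bias of a 6-month test when counts are missing.** Neither the correlation rho between the two counts nor the missingness pattern is given. Assume roughly normal counts with SD 15, rho of 0.3 to 0.7, and, in one arm only, the lowest quarter at 3 months missing the 6-month count ten times as often as the rest. If a fraction a is missing in the lowest quarter and b in the rest, the total is m = 0.25a + 0.75b. The complete-case mean in that arm shifts upward by

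15 × rho × 0.318 × (a − b) / (1 − m),

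where 0.318 is the standard normal density at the lower quartile.

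- a = 30%, b = 3%: m = 9.75%. 0.318 × 0.27 / 0.9025 = 0.095. Shift = 0.43, 0.71 and 1.00 points at rho 0.3, 0.5 and 0.7. A simulation of the same case gave 0.45, 0.73 and 0.99.
- Scaled to 4% missing: b = 0.04 / 3.25 = 1.23%, a = 12.3%. 0.318 × 0.111 / 0.96 = 0.037. Shift = about 0.17, 0.28 and 0.39 points.

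If both arms had the same pattern, the shifts would cancel in the difference. Here missingness depends only on the observed 3-month count, so a likelihood model that includes that count removes the shift.

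**Precision at 6 months from recovered counts.** Assume every patient without a 6-month count has a 3-month count, at equal rates in both arms. With fraction d missing, effective n = n observed / (1 − rho² × d).

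| Missing | Observed per arm | Effective n, rho 0.5 / 0.7 | Power, observed | Power, rho 0.5 / 0.7 |
|---|---|---|---|---|
| 4% | 240 | 242.4 / 244.8 | 95.5% | 95.6% / 95.8% |
| 10% | 225 | 230.8 / 236.6 | 94.2% | 94.7% / 95.2% |
| 15% | 212.5 | 220.8 / 229.4 | 93.0% | 93.9% / 94.6% |

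**Hospital term.** The ICC is not given. The standard error is multiplied by the square root of (1 − ICC): 0.990, 0.975 and 0.949 at ICC 0.02, 0.05 and 0.10, a cut of about 1% to 5%.

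**Averaging the two visits.** The mean of two counts has (1 + rho)/2 of the variance of one. The difference detectable with 95% power is 5 × √((1 + rho)/2) = 4.03, 4.33 and 4.61 points at rho 0.3, 0.5 and 0.7. A plain t-test on each patient's average gives the same figures when both counts are present.

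**The case against.** The strongest reply is that the quoted sentence is a general line on continuous variables in a condensed article. It does not say that visits are tested separately, that patients with one count are excluded, or that hospital is ignored in a fuller plan. Testing each visit would use every count obtained, and a t-test on cumulative or averaged adherence is not ruled out. All of this stands, so the documents do not show that data are discarded. Still, the article does name its tests and names none that handles two counts per patient. A cumulative or averaged value would also need a rule for patients with only one count.

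A reader might infer that using both counts is worth a third more patients, since 1/0.75 = 1.33 at rho 0.5. The documents do not support crediting that to the model. The gain comes from declaring the two-visit average as the contrast. With complete data and leaving hospital aside, the proposed model's 6-month contrast is simply the difference in 6-month means, as in the t-test, because the 3-month count is itself measured after randomisation.

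The missingness scenario is also fair to challenge. It is one-sided and assumed, and its larger version has more than twice the planned 4% missing. At 4% the shift is at most about 0.4 points. Finally, with individual randomisation and no stated stratification by hospital, the unadjusted test needs no hospital term to be valid.

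**Conclusion.** The point holds as an improvement in robustness and efficiency. A test at one visit leaves out randomised patients whose other count is held, and telephone visits in an open-label trial make missing counts above 4%, and unequal between arms, plausible. Under the assumed one-arm pattern the affected mean is about 0.2 to 0.4 points too high at 4% missing and 0.4 to 1.0 at about 10%, against a 5-point target. In the control arm this bias runs against the app.

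The precision gain is modest: about 1% to 5% of the standard error from a hospital term, and about 0.2 to 0.3 percentage points of power from recovered counts at 4% missing. The fall in detectable difference from 5.0 to 4.0–4.6 points applies only if the two-visit average is the declared contrast.

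It would be wrong to conclude that the named tests are invalid or the trial underpowered. With complete data the unadjusted comparison is valid, and 234 per group gives 95% power on the stated inputs. The correlation, the ICC and the missingness pattern are all assumptions.

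**What to change.** Analyse the primary endpoint with one linear model on both pill counts: arm, visit, arm-by-visit and hospital, with unstructured within-patient covariance and robust standard errors. Include every randomised patient with at least one count. Declare one primary contrast in advance, either 6 months or the average over both visits, and report it with its 95% CI. Keep the t-test or rank test as a sensitivity analysis.

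This changes analysis wording only and needs no new data. The small downside is that the model assumes missing counts are explained by observed data. That is weaker than what the complete-case test needs, but it can still fail.

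### The protocol expects user status to predict adherence but leaves it out of the primary comparison; adjusting for it is free, and the subgroup analysis needs an interaction estimate

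*Protocol article*

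**What the plan says.** The primary outcome is continuous, a pill-count percentage: "The primary endpoint is edoxaban adherence by pill count measurement at second (3 months) and third (6 months) visits" (Study endpoints and follow-up). For outcomes of this kind the Statistical analysis section states that the Student's "t-test and Kruskal-Wallis test will be used to compare continuous variables", the choice depending on normality. Neither test carries a covariate. The same section then adds: "Since new drug users might have a lower adherence than continuous users, subgroup analysis will also be performed on the new and continuous users".

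The sample size section assumes that "drug adherences would be 90% in the control group and 95% in the intervention group", one figure per arm and none by user status. It also states: "A sample size of 234 patients in each group achieves 95% power", this being the power "to detect a mean difference of 5.0 with a known SD of differences of 15.0". Patient recruitment and randomisation describes 1:1 central allocation and mentions no stratification by user status. The protocol gives neither the expected share of new users nor the size of the adherence gap.

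**The concern.** The reason given for the subgroup analysis is that the level of adherence may differ between user types. A difference in level is prognostic, and the direct way to use a prognostic factor is a term in the primary model. A subgroup analysis answers another question: whether the effect of the app differs.

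Two things are at stake. The primary estimate carries random error that a recorded baseline variable could remove. And if the two subgroups are later read by whether each reaches p<0.05, one significant and one non-significant result could be taken to show that the app works in one user type only. The trial is meant to inform a full-scale study, so that misreading could carry over into its design.

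**Working it through.** **Inputs from the protocol (Sample size calculation).** Difference 5.0 points, SD 15.0, two-sided alpha 0.05, power 95%, 234 per arm.

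**Assumptions, not in the protocol.** Share of new users f = 10% to 50%; adherence gap between user types d = 5 or 10 points.

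**1. Reproduce the stated size.** n per arm = 2 × 15² × (1.960 + 1.645)² / 5² = 450 × 13.0 / 25 ≈ 234. This is the formula for two independent groups, with 15 read as the SD between patients. That reading is used below, although the text speaks of a paired test and an SD of differences.

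**2. Gain from adjustment.** R² = f(1 − f)d² / 15². The adjusted SD is 15 × √(1 − R²), and the required n falls by the factor (1 − R²). The random error that imbalance in user status adds to the unadjusted difference has SD d × √(f(1 − f) × 2/234).

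| d | f | R² | n per arm for 95% power | Power at 234 | SD of imbalance error (points) |
|---|---|---|---|---|---|
| 5 | 10% | 0.09 × 25/225 = 1.0% | 232 | 95.2% | 0.14 |
| 5 | 50% | 0.25 × 25/225 = 2.8% | 228 | 95.5% | 0.23 |
| 10 | 10% | 0.09 × 100/225 = 4.0% | 225 | 95.7% | 0.28 |
| 10 | 50% | 0.25 × 100/225 = 11.1% | 208 | 96.9% | 0.46 |

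For scale, the standard error of the unadjusted difference is 15 × √(2/234) = 1.39 points.

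**3. Why the gap is not taken beyond 10 points.** With a 50:50 split and a control mean of 90%, a 15-point gap puts control means at 82.5% and 97.5%. A uniform 5-point effect would then put continuous users on the app at 102.5%, more than one pill a day on average under a once-daily regimen. A 10-point gap (85% and 95%) already reaches 100%.

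**4. Subgroups with an identical true effect.** Power in a subgroup with m patients per arm is Φ(5 / (15√(2/m)) − 1.96). With powers p₁ and p₂, the chance that exactly one subgroup is significant is p₁(1 − p₂) + p₂(1 − p₁).

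- At f = 50%, m = 117 in each: Φ(2.55 − 1.96) = 0.722, and 2 × 0.722 × 0.278 = 0.40.
- At f = 10%, m = 23.4 and 210.6: powers 0.206 and 0.928, and 0.206 × 0.072 + 0.928 × 0.794 = 0.75.

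| f | Power, new users | Power, continuous users | Exactly one significant |
|---|---|---|---|
| 10% | 21% | 93% | 75% |
| 20% | 36% | 90% | 61% |
| 30% | 51% | 86% | 50% |
| 40% | 63% | 80% | 43% |
| 50% | 72% | 72% | 40% |

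This takes an SD of 15 within each subgroup. If part of the 15 is itself the gap between user types, the chance is somewhat lower. At d = 10 and f = 50% the within-group SD is 15 × √0.889 = 14.1, power is Φ(2.70 − 1.96) = 0.77, and 2 × 0.77 × 0.23 ≈ 0.35.

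**5. Interaction test.** The standard error is 15 × √(2/m₁ + 2/m₂): 2.77 points at f = 50% and 4.62 at f = 10%. Power for a 5-point difference in effect is 44% and 19% respectively. The difference detectable with 80% power is 7.8 and 13.0 points.

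**The case against.** The strongest reply is that nothing here is invalid. Allocation is central, concealed and 1:1, so the unadjusted difference is unbiased with a sound type I error, and chance imbalance is already reflected in its standard error. The trial has 95% power before any adjustment, and no decision turns on one or two further percentage points. All of this stands. A reader might infer that omitting user status biases the result; the documents do not support that.

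A reader might also infer that the protocol commits itself to separate subgroup p-values and to a claim based on them. It does not: it announces a subgroup analysis and fixes neither method nor rule, and an analysis plan that is not shown may supply both. Nor is the subgroup question idle. Near a ceiling of about 100%, patients who start lower have more room to improve, which is a fair reason to look for a different effect. The protocol also says only that new users might adhere less.

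Discordance in significance should not be confused with opposite effects. With the same true effect, estimates of opposite sign occur in only about 1% to 13% of trials over the same range of f. With no effect at all, exactly one subgroup is significant in 2 × 0.05 × 0.95 = 9.5%.

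Finally, the trial runs at 10 hospitals, but no centre effect is given, so a centre term is a matter of choice. What remains is that the tests named for the primary outcome cannot use a factor that the same section singles out.

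**Conclusion.** The point holds as a modest, costless improvement to a stated method. It is not a flaw in validity. Adjustment for user status would remove about 1% to 3% of the outcome variance for a 5-point gap and 4% to 11% for a 10-point gap, at most 26 fewer patients per arm (234 − 208) for the same power. These figures rest on the assumed share of new users and the assumed gap.

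The interaction recommendation is a safeguard against a foreseeable misreading. With the protocol's own effect, SD and size, one subgroup significant and the other not is an ordinary result of chance, about 40% to 75% of the time, even when the app works equally well in both. The interaction test is itself weak here, so a non-significant interaction would not show that the effects are equal.

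**What to change.** - **Primary analysis.** At each of the two stated visits, estimate the treatment difference from a linear model of adherence on treatment and user status (new or continuous, defined at baseline). Report the adjusted mean difference with its 95% CI. A centre term is optional.
- **Skewed adherence.** Replace the switch between tests by robust or bootstrap standard errors, or keep a rank-based comparison as a sensitivity analysis.
- **Subgroups.** Label them exploratory, report both effects with CIs, and base any claim of a differing effect on the treatment-by-user-status interaction, reported with its own CI and a note on its limited power.

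The cost is a few sentences of analysis wording, settled before outcome data by arm are examined. User status is already needed for the planned subgroup analysis, so no new data or patients are required.

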### Ethics and dissemination

This study was approved by the institutional review board of Seoul National University Bundang Hospital and will be conducted according to the principles of the Declaration of Helsinki. The potential risks to participants are negligible in this study. The participants will be handed study information sheets and asked to provide written informed consent. The study results will be disseminated via publication in a reputable journal and presentation at scientific meetings. Individual participant data that underlie the results reported (text, tables, figures and appendices) will be shared after deidentification process on reasonable request.

## Discussion

This randomised control trial investigates the feasibility and efficacy of using a smartphone app to improve adherence to anticoagulation therapy (edoxaban). Furthermore, this study will also assess the influence of app-based interventions influences on the reduction of AF-related adverse clinical events. Today, smartphones have became an integral part of everyday life. We believe that our study will be helpful when formulating public health strategies for improving NOAC adherence using smartphones.

All participants in the intervention group will be asked to input the measured BP and HR data on a smartphone, in addition to responding to a push alarm for taking their medication. The recognition of the irregular rhythm of AF during HR measurement could remind the participants of the necessity of anticoagulation therapy, which they will be informed about by their physician during the education session. Feedback questions to remind the patient of their BP control status might further reinforce disease awareness and drug adherence. The stored information could also be used as a reference to set an optimal therapeutic goal for education and medication control.

A similar study was performed with NOACs, using a telemonitoring system accompanied by personal telephone feedback.^12^ In that study, although the telemonitoring system achieved high drug adherence (over 90%), it was not cost-effective. The human resource and system setup costs to operate telemonitoring-based feedback impeded the wide usage of this method in clinical practice. Digital interventions using smartphone apps are becoming an increasingly common way to support medication adherence and self-management in chronic disorders.^27^ Smartphones also help to improve access to cardiac rehabilitation and heart failure management for patients unable to attend traditional centre-based cardiac rehabilitation^28^ We believe that our strategy of using a smartphone app would be an effective way to increase drug adherence at a minimum cost.

As with other current management strategies, apps can evolve into tailored programmes. Besides the simple reminders, this strategy can be incorporated into a multimodal strategy that results in sustained improvements in adherence.^29^ Reminders primarily focus on unintentional non-adherence, identifying the reasons for non-adherence and developing a scale that assesses unintentional non-adherence.^30–32^ This randomised trial will not only evaluate the effectiveness of the reminder app on disease awareness and drug adherence in patients with AF but will also try to find components that may hinder patient adherence to NOACs. This information could be used to develop a strategy to ensure sustained improvement in adherence to current medical therapy.

